### Study outcomes

2.9

#### Primary measures

2.9.1

The primary outcome is a change in MetS markers (BP, TG, WC, FBG and HDL) in Ghanaian adults with T2DM who participate in a 12‐week PA programme, compared to those who receive usual diabetes care.

#### Secondary measures

2.9.2

Secondary outcomes are: (a) a change in QoL in Ghanaian adults with T2DM who participate in a 12‐week PA programme, compared to those who receive usual diabetes care, (b) feasibility of implementation, determined by measures of safety (c) feasibility of implementation, determined by measures of participation.

### Data collection

2.10

The following data will be collected.

#### Demographics

2.10.1

Personal information will be collected including age, education, income, marital status, sex and employment. Data will be collected using the Demographic Questionnaire. This data will be collected by a member of the research team during the baseline visit.

#### Medical history

2.10.2

Data relating to current medications and medical conditions will be collected during the baseline visit and recorded on the medical clearance report.

#### Quality of life assessment

2.10.3

Quality of life will be assessed using the Short Form Health Survey, version 2 (SF‐12 V2). This tool has 12 items that measure a person's subjective view of their functional health and general well‐being. It measures the following eight specific health domains, including physical functioning, social functioning and mental health. It is assessed based on a 0–100 score in each domain as well as the physical component summary (PCS‐12) and the mental component summary (MCS‐12) (Ware et al., 2002). A higher score indicates high well‐being and vice versa. The questionnaire has good reliability and validity, with an established Cronbach's alpha of 0.82 and 0.81 for PCS and MCS, respectively (Lam et al., 2013). QoL data will be collected at baseline and the 12‐week follow‐up visit.

#### Physical activity level

2.10.4

Participants will be assessed for their level of PA (e.g., amount of time they undertook PA, type of PA) in the last 7 days using IPAQ (Craig et al., 2003). This data will be collected during the screening visit, to determine if they are sedentary (i.e. not achieving at least 600 metabolic equivalent of task – minutes/week based on the IPAQ assessment). PA level will also be measured at the end of week 12. The validity and reliability of the IPAQ—SF were assessed in a study conducted in 12 different countries (Craig et al., 2003). South Africa was the only African country included in that study. The study found a total reliability coefficient correlation (Spearman's rho) of 0.84 per total MET/ week across the PA domains.

#### Physical, clinical and biochemical data

2.10.5

Blood pressure and heart rate will be taken during the baseline visit for all participants and during each exercise session at the physiotherapy department for participants in the IG group. Blood pressure will also be measured at the 12‐week follow‐up. WC will be measured at baseline and at the 12‐week follow‐up. A blood sample will be collected at baseline and at the 12‐week follow‐up to measure Fasting Blood Glucose (FBG), high‐density lipoprotein (HDL) and triglycerides (TG).

#### Exercise participation and complications

2.10.6

Data regarding participation in the PA programme will be collected. This includes the type of exercise, duration, intensity and frequency of those exercises. Data regarding exercise‐related complications will also be collected. The PT will collect such data from participants in the IG each week during their visit to the physiotherapy department and during the week‐12 follow‐up visit.

#### 6‐Minute walk test

2.10.7

The PT will take participants through a *6‐Minute Walk Test* (6MWT) to test their exercise capacity at baseline and 12‐week follow‐up. It assesses baseline functional capacity and cardiovascular risk, which are necessary in prescribing exercise intensity for patients (Amaricai, 2020). The walk test supports the prescription of an effective and safe exercise programme for people with T2DM (Nolen‐Doerr et al., 2018). A study among patients with T2DM showed a high interclass correlation coefficient for the 6MWT (Alfonso‐Rosa et al., 2014).

#### One‐repetition random motion test

2.10.8

Each participant will be assessed for one‐repetition maximum in each of the resistance exercises. When using a TheraBand, 1RM is measured based on band extension from its original length. A 50%, 75% and 100% increase in band length corresponds to 1.5 kg, 1.9 kg and 2.7 kg, respectively (Kwon et al., 2010). This test will be done at baseline.

### Data collection procedure

2.11

Data relating to demographics, eligibility screening, PA levels and QoL will be collected using online questionnaires. A nurse or research team member who is independent of the participant's care team will provide the participant with a quiet place at the NDMRC and administer the eligibility screening checklist. Similarly, the nurse will follow the same procedure to administer the baseline demographic data questionnaire and the baseline and week‐12 follow‐up IPAQ—SF and SF‐12V2 questionnaires. If a participant is unable to read and/or write in English, the nurse will administer the questionnaires verbally in the local language. Surveys will be completed electronically via a RedCap survey tool.

Prior to each exercise session at the physiotherapy centre, the PT will measure the IG participants' BP, HR and random blood glucose (RBG) using the hospital's standard procedure.

WC will be taken by measuring the mid‐point between the lower costal margin and iliac crest.

A 5‐mL sample of venous blood will be collected after at least an 8‐h overnight fast. Participants will be advised about the need for the overnight fast in the PICF and will be sent a reminder via text. A senior biomedical scientist will collect blood samples and biochemical tests (TG, HDL and FBG) will be performed using the hospital's standard protocol. Blood sample will be collected into a serum separation tube and analysed using a dry chemistry analyser.

During the participants' weekly visit to the physiotherapy department, the PT will assess exercise participation and safety using a checklist for exercise participation and the participants' exercise diary. Measures of participation will be determined by the percentage of sessions attended and the proportion of participants who complete the prescribed PA: 22 sessions of home‐based aerobic exercises and 14 sessions of facility‐based resistance training. An overall score <50% of attendance will be judged as low participation and above 70% will be graded as high participation. A score between 50% and 70% will be graded as moderate participation. Reasons for non‐participation or withdrawal will be documented.

Safety outcomes will be assessed by examining participant's subjective reports relative to possible pain, injury, medical emergencies and other exercise‐related complication that may be encountered during participation in the PA program. Safety and participation rate will be assessed as a composite of any adverse events recorded as part of the PT's checklist for exercise participation and safety and the participants' exercise diary.

At the end of each training session, the Borg Rating of Perceived Exertion (RPE) scale will be used to assess perceived exercise tolerance and exercise fatigue (Liguori et al., 2021). Schedule of visits for the RCT are outlined in Figure 1.

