#### The intervention group

2.8.1

Participants allocated to the IG will engage in a 12‐week PA programme comprising aerobic exercise and resistance training, in addition to their usual diabetes care. The exercise goal will be at least 120 min/week of exercise distributed over at least 3 days/week. In total, participants in the IG will be asked to engage in 36 sessions of exercise over the 12‐week period, with each session lasting between 35 and 45 min. Of the 36 exercise sessions, 14 individualised sessions will be conducted at the physiotherapy department of the Korle‐Bu Teaching Hospital. The remaining 22 exercise sessions will be self‐delivered at home. Each exercise session will be structured as follows:
3 min of warm‐up (stretching exercises);10 min of resistance exercise (exercises targeting upper and lower large body muscles using TheraBand). The specific resistance exercise prescribed in this program will be: chest press, shoulder curls targeting the upper body muscles, and leg press targeting lower body muscles;20–30 min of aerobic exercise (walking) at moderate pace (4.5–5.1 km/h = 3.5 MET) or brisk pace (5.2–5.6 km/h = 4.3 MET) (Ainsworth et al., 2011); and2 min of cool‐down (stretching exercises).

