### Limitations

4.1

A limitation of this study is that it is a single‐site feasibility RCT, which is part of a PhD project with limited resources, time and funding. Another limitation is that there is no sample size calculation. We adopted an a priori, which recommended a sample size of *n* = 72 (36 per arm), thereby limiting the generatability of the findings to other study settings. Further, due to limited funding, objective PA assessment, such as the use of pedometers could not be utilised. Therefore, home‐based exercises will be assessed based on subjective reports from participants.

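### The completion measure in section 2.11 counts home aerobic and facility resistance sessions, but section 2.8.1 puts both components in every session

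*Protocol article*

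**What the plan says.** Section 2.8.1 of the protocol article asks intervention participants for "36 sessions of exercise over the 12‐week period, with each session lasting between 35 and 45 min". It divides these sessions by place only: "Of the 36 exercise sessions, 14 individualised sessions will be conducted at the physiotherapy department", and "The remaining 22 exercise sessions will be self‐delivered at home". It then gives one template, introduced by "Each exercise session will be structured as follows": 3 min warm-up, 10 min resistance, 20–30 min walking and 2 min cool-down. The week 1 text (all sessions at the facility) and the week 2 to 12 text (two home sessions and one facility session a week) both list walking and resistance together. The hypoglycaemia advice for home sessions also covers the order of resistance and aerobic work, so it expects both at home.

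Section 2.11 names two participation measures: the percentage of sessions attended, and the proportion of participants completing the prescribed activity. It describes that activity as "22 sessions of home‐based aerobic exercises and 14 sessions of facility‐based resistance training". Attendance is then graded, starting with "An overall score <50% of attendance will be judged as low participation", with moderate from 50% to 70% and high above 70%.

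Later in section 2.11: "Safety and participation rate will be assessed as a composite of any adverse events recorded", with the therapist's checklist and the exercise diary as sources. Section 2.9.2 lists safety and participation as separate secondary outcomes.

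**The concern.** The session counts in sections 2.8.1 and 2.11 agree, but the content does not. Section 2.8.1 separates sessions by place. Section 2.11 also separates them by type of exercise, so home resistance and facility walking drop out of its description of the prescribed activity.

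Participation is one of the two feasibility measures, and the trial is meant to inform a larger one. Two analysts with the same data could report different completion rates, one following section 2.8.1 and the other section 2.11. The part most exposed is unsupervised resistance work at home. Under section 2.11 a favourable completion rate could be reported without any of it having been done.

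The composite sentence is a lesser problem in the same section. Attendance is not an adverse event, so a participation rate cannot be computed from adverse events.

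**Working it through.** **Inputs, all from the protocol article**

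- Week 1: 3 sessions, all at the facility, each with 20 min walking and 10 min resistance (section 2.8.1, week 1).
- Weeks 2 to 12: 11 weeks, each with 1 facility and 2 home sessions of 30 min walking and 10 min resistance (section 2.8.1, week 2 to week 12).
- Warm-up 3 min, cool-down 2 min (section 2.8.1).
- Completion definition: 22 home aerobic and 14 facility resistance sessions (section 2.11).

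**Step 1: reproduce the plan's own figures**

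- Facility: 3 + 11 × 1 = 14. Home: 11 × 2 = 22. Total: 14 + 22 = 36. All three agree with the article.
- Shortest session: 3 + 10 + 20 + 2 = 35 min. Longest: 3 + 10 + 30 + 2 = 45 min. The stated 35–45 min range is obtained only when a session holds both components.

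**Step 2: component bouts**

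Under section 2.8.1 each of the 36 sessions has one walking and one resistance bout, so 2 × 36 = 72 bouts are prescribed.

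| Component | Prescribed (2.8.1) | Counted (2.11, literal) | Not counted |
|---|---|---|---|
| Walking | 36 | 22 (61%) | 14 (39%), all at the facility |
| Resistance | 36 | 14 (39%) | 22 (61%), all at home |
| Both | 72 | 36 (50%) | 36 (50%) |

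**Step 3: main-exercise minutes (warm-up and cool-down left out)**

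- Walking prescribed: 3 × 20 + 33 × 30 = 1,050 min. Counted: 22 × 30 = 660 min; 660/1,050 = 63%.
- Resistance prescribed: 36 × 10 = 360 min. Counted: 14 × 10 = 140 min; 140/360 = 39%.
- Together: (660 + 140)/(1,050 + 360) = 800/1,410 = 57%.

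A participant who did exactly what section 2.11 lists, and nothing more, would therefore be a full completer with 50% of the component bouts and 57% of the main-exercise minutes prescribed in section 2.8.1.

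**Step 4: which measure is affected**

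Percentage attended has a denominator of 36 under either section, provided a session counts as attended whatever was done in it. Its value and grade do not then depend on the component labels. Only the completion proportion does.

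**The case against.** The strongest reply is that the labels in section 2.11 are loose shorthand for home and facility sessions, and that the outcome is descriptive, with no test or progression rule attached. Section 2.10.6 plans to record exercise type, duration, intensity and frequency, so component-level completion can be derived and no data need be lost. This reply stands in part: it limits the consequence and makes the correction cheap. It does not say which section governs, and the shorthand reading is nowhere stated.

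Several stronger readings are tempting, but the document does not support them.

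- *The whole participation outcome is wrong.* It is not. The attendance percentage and its grades survive, as step 4 shows.
- *Completion of all 36 sessions will be near zero whatever the adherence.* If each session is done independently with the same probability p (an assumption), the chance of completing all 36 is p^36: 2.3% at 0.90, 15.8% at 0.95, 48% at 0.98 and 70% at 0.99. The result depends on p, and clustering of adherence within people would raise it at the same mean. The article gives no adherence figure.
- *The attendance grade is distorted.* All facility and no home sessions gives 14/36 = 38.9% (low); the reverse gives 22/36 = 61.1% (moderate). Both follow from the 14:22 split and would be unchanged by correcting the labels.
- *Reliance on self-report is a hidden flaw.* Section 4.1 discloses it for home exercise and attributes it to limited funding.
- *The above-70% grade should define a completer.* Section 2.11 uses that cut for high participation, not for completion.

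On the composite sentence, the sections around it define safety and participation separately. That makes it a wording fault that adds little weight.

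**Conclusion.** The contradiction is real and nothing in the article resolves it; the participant flow figure is not shown and was not used. Sections 2.8.1 and 2.11 describe different prescribed programmes, and the completion proportion depends on which is followed. At the extreme, full completion under section 2.11 equals 50% of the component bouts, or about 57% of the main-exercise minutes, in section 2.8.1. These figures assume a literal reading of section 2.11, one bout of each component per session, and the stated 20 and 30 min walking times. They describe the widest gap the wording allows and do not predict what participants will do.

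The defect is confined to one of two participation measures within a descriptive secondary outcome, and it can be corrected from data already planned. It should be fixed before the data are analysed. It does not threaten the trial as a whole.

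**What to change.** 1. Reconcile section 2.8.1, including its week 1 and week 2 to 12 parts, with section 2.11 on what each home and facility session contains. Which content is right is for the sponsor to decide.
2. Define completion in section 2.11 by component, so that it matches the reconciled prescription, using the type and duration data planned in section 2.10.6.
3. Tally resistance and walking separately for home and for facility sessions, and align the therapist's checklist and the exercise diary with this.
4. State that percentage attended counts sessions out of 36 whatever their content, if that is the intention.
5. Reword the composite sentence in section 2.11 so that safety and participation are assessed separately, as section 2.9.2 lists them.

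The cost is some rewording and a small change to the checklist and diary. Reported completion may be lower than under the literal section 2.11 definition; the document gives no basis for saying by how much.

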### Eligibility criteria

2.4

For participants to be included in the study, they must: (a) have a diagnosis of T2DM; (b) have MetS; (c) receive medical clearance provided by their physician to participate in the exercise programme; (d) have resided in Ghana for at least 2 years; (e) be at least 18 years of age and (f) be sedentary (not achieving 600 metabolic equivalent of task – minutes/week), based on the International Physical Activity Questionnaire – short form (IPAQ‐SF) assessment (Craig et al., 2003).

The following are the exclusion criteria: (a) current medical conditions that preclude physical activity (e.g., significant cardiac/respiratory diseases, severe osteoarthritis or arthritis, angina episodes during rest or with minimal exertion, significant vision loss and limb amputation); (b) frailty index score >3; (c) inability to travel to the NDMRC for supervised training; (d) no access to a mobile phone; or (e) pregnancy.

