##### Week‐1

In Week‐1, all three training sessions will be done at the physiotherapy department of the Korle‐Bu Teaching Hospital under the supervision of a PT. The reason for the supervised exercise session is to ensure that participants can perform each type of exercise correctly and within the recommended safety standards. At the start of week 1, participants will be assessed to confirm that they are well enough to participate. Each participant will be assessed by the PT for the following measures: (a) FBG, (b) BP and (c) HR. Target HR will be based on the recommended safe range of 64%–76% of maximum heart rate, which is determined by subtracting the participant's age from 220 (Physical Activity Guidelines Advisory Committee, 2009; Riebe et al., 2018). Exercise in week 1 will be limited to 35 min (20 min of walking and 10 min of resistance training plus 5 min of warm‐up and cool‐down) targeting 50%–60% of maximum heart rate.

To prevent the incidence of hypoglycaemia, participants will be advised, during the education session, on the common symptoms of hypoglycaemia, such as abnormal sweating, shakiness, visual disturbance weakness, headache and confusion. Where a participant experiences such symptoms, the participant is instructed to stop the training immediately, take a rest and eat immediately. To prevent hypoglycaemia during exercise sessions at home, participants were also advised on recommended strategies such as not exercising beyond the recommended intensity and time limits (Fahey et al., 2012), performing resistance exercise before aerobics (Colberg et al., 2016) and injecting insulin at least 60 min prior to exercise (for those using insulin) (Koivisto & Felig, 1978). During the weekly exercise sessions at the physiotherapy department, the PT utilised the glucose management strategy recommended by Riddell et al. (2017). Guided by the strategy, if a participant's starting glycaemia is less than 90 mg/dL, they will be instructed to take 10–20 g glucose and delay exercise until glycaemia is greater than 90 mg/dL. If a participant's glucose is between 90 and 124 mg/dL, they will be instructed to take 10 g of glucose. Participants were not allowed to exercise if their starting glycemia was above 270 mg/dL.

##### Week 2 to week 12

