Exercise will be adjusted to 45 min (30 min of walking and 10 min of resistance training plus 5 min of warm‐up and cool‐down) at 75% of maximum heart rate. Participants will continue to engage in three exercise sessions per week, having two sessions self‐administered at home and one supervised session at the physiotherapy department, with no 2 days without exercise.

Resistance training will be graduated from 60% one‐repetition maximum (1RM) and progress to 100% IRM based on the assessment by the PT. The one‐repetition maximum measure refers to how much weight the participant can lift in one repetition. Participants will perform a single set of resistance exercises with 8–12 repetitions, with a between‐set resting interval of 90–120 s.

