## DISCUSSION

4

Interventions aimed at controlling MetS markers in people with T2DM are a priority (Longo‐Mbenza et al., 2010). Despite the integral role PA plays in modifying MetS markers, the problem of meeting recommended PA targets remains a challenge for people with T2DM (Oyewole et al., 2014). A significant proportion of Ghanaian adults with T2DM may be considered high‐priority population due to some health beliefs that influence their health‐seeking behaviours, including PA uptake. For instance, Korsah et al. (2022), in assessing the experiences and cultural beliefs of Ghanaians with diabetes, found that some people perceive their diabetes diagnosis as a spiritual disease that can only be treated through spiritual healing. There is also some evidence that many people in Ghana first seek herbal and faith‐based treatment and only resort to biomedical treatment when the disease persists (Arias et al., 2016). These evidences suggest that PA is perceived as less important in managing diabetes. The education component of the PA programme to be evaluated in this study aims at addressing the poor understanding and other barriers that exist in engaging in a PA programme. Also, lack of access to exercise facilities and the cost to access them appear to be major barriers to PA uptake (Higgerson et al., 2018). The PA programme to be evaluated is expected to be suitable for people in low‐resource communities because it is home‐based with no access cost.

A feasibility RCT is usually intended to guide the planning of a future definitive investigation, as it helps to establish an effect and variance (Thabane et al., 2010). This study has the potential to provide information on efficacy, intervention participation and safety (Eldridge et al., 2016; Thabane et al., 2010). Thus, the findings will inform future trials on study design, relevant resources, trial personnel and data management (Thabane et al., 2010). The results of this feasibility study will provide preliminary evidence regarding the effect of a culturally appropriate PA programme and whether it will show a trend towards improvement in MetS markers and QoL in Ghanaian adults with T2DM. The findings of this study will also prove the feasibility or otherwise of the PA programme, prior to its full implementation in the population.

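### The only participation grade pools hospital and home sessions, so a high grade can sit on home completion of only 55%

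*Protocol article*

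**What the plan says.** The title and Introduction call the programme home-based, and evaluating its feasibility is a stated secondary objective. Secondary measures (2.9.2) makes participation one of the feasibility outcomes.

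The programme itself is mixed. Section 2.8.1 states: "Of the 36 exercise sessions, 14 individualised sessions will be conducted at the physiotherapy department". It continues: "The remaining 22 exercise sessions will be" done by participants at home. In week 1, "all three training sessions will be done at the physiotherapy department". From week 2 to week 12 there are two home sessions and "one supervised session at the physiotherapy department" each week.

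Data collection procedure (2.11) names two participation measures. One is the percentage of sessions attended. The other is the share of participants who complete the prescribed activity, listed as 22 home and 14 facility sessions. Cut-offs are attached to one figure only: "An overall score <50% of attendance will be judged as low participation and above 70% will be graded as high participation". Scores from 50% to 70% are moderate.

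Three other statements bear on how the grade will be read. Limitations (4.1) says that home exercise is assessed from participants' own reports. Eligibility criteria (2.4) lists as an exclusion "inability to travel to the NDMRC for supervised training". The Discussion expects the programme to suit low-resource communities "because it is home‐based with no access cost".

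**The concern.** For a programme presented as home-based, a future trial team will want to know whether patients do the home sessions. The one graded result does not isolate this. Nearly two-fifths of the score comes from supervised visits observed by the physical therapist, and the rest comes from self-report. Good clinic attendance can therefore carry the grade while home completion is modest or poor. Good home completion with few visits can be graded lower. A report of high participation could then be taken as evidence of home feasibility, and carried into the design of the larger trial, when the home sessions on their own would be graded lower.

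**Working it through.** **Inputs.** Week 1: 3 hospital sessions, 0 home. Weeks 2 to 12 (11 weeks): 1 hospital and 2 home sessions per week. Cut-offs from 2.11: low below 50%, moderate 50% to 70%, high above 70%.

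**Reproducing the protocol's session count.** Hospital: 3 + 11 × 1 = 14. Home: 11 × 2 = 22. Total: 36. This matches 2.8.1. The hospital share of the score is 14/36 = 38.9%.

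**Pooled score.** Score = (hospital attended + home done)/36. High needs more than 0.70 × 36 = 25.2, so at least 26 sessions. Leaving low needs at least 0.50 × 36 = 18 sessions. The table compares this with the same cut-offs applied to home sessions alone (home done/22).

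| Hospital | Home | Pooled score | Pooled grade | Home alone | Home grade |
|---|---|---|---|---|---|
| 14/14 | 12/22 | 26/36 = 72.2% | high | 54.5% | moderate |
| 14/14 | 4/22 | 18/36 = 50.0% | moderate | 18.2% | low |
| 3/14 | 22/22 | 25/36 = 69.4% | moderate | 100% | high |
| 4/14 | 22/22 | 26/36 = 72.2% | high | 100% | high |

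The first and third rows are in the wrong order as regards home completion.

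**How far the grade can be off.** A high home grade needs more than 0.70 × 22 = 15.4, so at least 16 home sessions.
- *Upward.* A pooled high with fewer than 16 home sessions requires at least 26 − 15 = 11 of 14 hospital visits. A low home grade (10 or fewer of 22) cannot become a pooled high, since 14 + 10 = 24 and 24/36 = 66.7%.
- *Downward.* For someone who attends the three week-1 visits, a high home grade cannot become a pooled low, since 3 + 16 = 19 and 19/36 = 52.8%.

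For such participants, a low home grade cannot become a pooled high, nor a high home grade a pooled low. Any discrepancy is one step.

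**Arm level.** The article does not say whether the grade applies to each participant or to the arm. With mean attendance of 95% at hospital and 55% at home, the score is (14 × 0.95 + 22 × 0.55)/36 = 25.4/36 = 70.6%, high. With 30% and 95%, it is (14 × 0.30 + 22 × 0.95)/36 = 25.1/36 = 69.7%, moderate.

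**Other readings of the overall score.** If it means the unweighted average of the two percentages, 14/14 with 12/22 gives (100 + 54.5)/2 = 77.3%, high, and 3/14 with 22/22 gives (21.4 + 100)/2 = 60.7%, moderate. The misordering remains. If attendance means hospital visits only, home sessions are not graded at all.

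**The case against.** The stated outcome is feasibility of the programme, which is openly a mix of hospital and home sessions. A pooled score is a legitimate measure of dose received, and this stands. The protocol also lists home and facility sessions separately in its completion measure and plans to record reasons for non-participation, so the setting is not ignored. This stands too, but the completion measure has no cut-off and does not qualify the grade. Feasibility outcomes are to be summarised descriptively (2.13) and no progression rule is tied to the grade, so it would be wrong to say that a go/no-go decision turns on it.

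A reader might infer more than the document supports in three ways.
- *That anyone who stops travelling can never be graded high.* Week 1 is entirely supervised and comes before any home session. On the 36-session reading, a participant who does all home sessions needs only one visit beyond week 1 to score 26/36 = 72.2%, high.
- *That excluding people unable to travel distorts the grade.* The exclusion is a normal consequence of a supervised component. It causes none of the misgrading and limits only the population to which the result applies.
- *That the Discussion contradicts the design.* Its remark about access cost follows a sentence on the cost of exercise facilities and is worded as an expectation. It needs qualifying, but it is not a claimed result.

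The home figure is also the weaker measurement. It rests on self-report, and the weekly review of the diary takes place at the hospital visit, so those who stop attending lose that check.

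**Conclusion.** The point holds in a limited form. The only graded participation result can mask modest or poor home completion: high at 55% home completion and moderate at 18%, each with full hospital attendance. It can also understate complete home participation, giving moderate at 100% with only the week-1 visits. The first pattern needs only good clinic attendance (at least 11 of 14 visits) and so is quite plausible. The last needs markedly uneven attendance. How often either would occur cannot be known from the document.

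The percentages assume that the score is sessions done out of 36 and that every home session is known to be done or not done. The misordering also survives the unweighted-average reading. The pooled score is not wrong in itself; the weakness is that it is the only graded evidence for a programme described as home-based. This is a modest, inexpensive correction to how feasibility is reported, and the trial's validity is not in question.

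**What to change.** In 2.11, keep the pooled score as the measure of total programme dose. Add that the existing cut-offs (below 50%, 50% to 70%, above 70%) will also be applied separately to the 22 home sessions and the 14 hospital sessions. Base any statement about home-based feasibility on the home-session grade, read with the self-report limitation in 4.1. In the Discussion, qualify the suitability statement to say that the programme includes weekly hospital supervision and is tested in people able to travel to the centre.

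The cost is one extra tabulation of data already being collected. The downsides are a home grade that depends on self-report, whereas the pooled score at least includes observed attendance, and a participation result that may look less favourable.
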